## Abstract

**Background:**

Offenders with a mental illness are routinely excluded from vocational services due to their mental health. Employment has shown to be very important in improving mental health, reducing recidivism, and connecting people to society. This study examines the effectiveness of an established intervention which is relatively untested in this population, Individual Placement and Support (IPS), to help offenders with mental health problems into competitive employment. The overall research question is whether IPS is effective in gaining and sustaining competitive employment for offenders with a Severe Mental Illness (SMI). The context is an English criminal justice setting across different populations. The study will also measure non-vocational outcomes such as recidivism, mental health and social stability.

**Methods/Design:**

A Realistic Evaluation (RE) design will address the questions “What works, for whom, and in what circumstances?” This study includes pre and post comparisons for a cohort of approximately 20 people taking part in IPS, and a similar number of controls, over a one year period. The RE also consists of interviews with practitioners and offenders in order to understand how IPS works and develops within the criminal justice system (CJS). By applying this framework the research can go from discovering whether IPS works, to how and why (or why not) IPS works. This is achieved by examining where the intervention is occurring (Context (C)), the mechanisms (M) that create particular behaviours, and how the outcomes (O) from the intervention all come together (CMOs). Employment outcomes will also be examined for all participants.

**Discussion:**

By applying RE the research will permit inferences to be drawn about how and why (or why not) IPS works, by examining context, mechanisms and outcomes. IPS has never been implemented within the CJS in the United Kingdom. As a result, this evaluative research will not only provide a novel insight into the core research areas, but also how the intervention can be improved for others in the future.

## Background

Mental illness could be defined as “health conditions that are characterised by alterations in thinking, mood, or behavior (or some combination thereof) associated with distress and/or impaired functioning” [1], p. 5. Only 7.3 % of people with severe and enduring mental health problems are in employment [2]. This is in stark contrast to the 73 % of those employed among the general population within the United Kingdom (UK) [3]. Furthermore, the gap between employment in the general population and people with any mental illness within England is 37.1 % [4]. In other countries, too, people with a mental illness are also up to 50 % more likely to be unemployed than those with other disabilities [5].

Employment figures are even worse amongst those within the Criminal Justice System (CJS). The Ministry of Justice (MoJ) has previously aimed to increase work opportunities within prisons, however this does not seem to be improving employment and/or opportunities to gain employment upon release [6]. For example, Niven and Stewart found that 70 % of working-age prisoners in England and Wales were found to have no form of employment and/or education upon release [7]. Even prior to entering prison, 67 % of prisoners have been shown to be unemployed [8]. Furthermore, in 2013/14, only 25 % of prisoners entered employment when released from prison [9] indicating that offenders are failing to attain the benefits-such as social engagement, economic stability and independence, which employment can offer them on their release.

The mental health of prisoners has been consistently worse by comparison with the general population [10, 11]. For example, an eminent study carried out within England and Wales by Singleton, Meltzer and Gatward found that some 90 % of prisoners were suffering from a mental health condition whilst more than 70 % had two or more mental health disorders [12]. Even though this research is more than a decade old, it was conducted within a population which has more than doubled within the last 20 years [13] and as a result now has one of the highest rates of imprisonment in Western Europe [14]. Recent figures indicate that 62 % of male and 57 % of female prisoners who are serving a sentence have a diagnosable personality disorder [15]. The proportion of males and females in prison who suffer from depression and anxiety is 23 % and 49 % respectively, while 25 % of female prisoners and 15 % of male prisoners also report symptoms indicative of psychosis [16]. This high prevalence of mental illness amongst prisoners is also reflected in the 23,183 reported self-harm incidents in the 12 month period ending December 2013 [17].

Consequently, it is reasonable to infer that there are more people in prison with mental health problems at present than ever before [18]. Indeed, research has consistently demonstrated prison environments to have a large number of prisoners with unmet mental health treatment needs [18–21].

These findings are a significant concern as employment has shown both to improve an individual’s mental health and quality of life [22], and to reduce re-offending by up to 50 % [8, 23, 24]. Research in the UK also indicates not only that the vast majority of offenders want to stop offending, but that they see employment as key to achieving this [25].

However, people with a mental illness and criminal justice involvement are often routinely excluded from resettlement vocational services due to their illness and thus are perceived to be ‘not ready for work’ [26]. A criminal history is also widely presumed to be a significant barrier due to the employers’ screening procedures for applicants [27]. The social stigma of a mental illness together with the criminal record held by individuals have been described as a “double jeopardy” [22], p. 1. The adverse effect of these barriers is further evidenced in that clients with a SMI and criminal justice involvement have delayed entry onto vocational services compared to those who do not have criminal justice involvement [28].

### The intervention: IPS

The IPS model consists of a set of core principles that have been extensively examined using continuous feedback from all those involved within the field; real world research data has also been utilised as a means to bring together service ideas, outcomes, and to best adapt to the needs of clients who have a SMI [29–33]. As a result, the IPS model has been extensively studied and developed internationally [34] and is now the leading evidence-based approach to supported employment for people who have a SMI [35]. There are currently eight features to the IPS model which are fairly self-explanatory, as follows [36]:Competitive Employment is the Primary GoalZero Exclusion: Eligibility Based on Client ChoiceIntegration of Employment & Mental Health ServicesAttention to Client PreferencesPersonalised Benefits CounsellingRapid Job SearchSystematic Job DevelopmentTime-Unlimited & Individualised Support

IPS has shown success rates in achieving competitive employment to be as high as 61 % using its ‘place-train’ approach, as opposed to 23 % using a common ‘train-place’ alternative method [36]. Overall, the substantial research within the literature suggests that around 60 % of those who take part in IPS gain competitive employment, with around 50 % becoming steady workers. Furthermore, the benefits of IPS also extend to improvements in the mental health of an individual following sustained employment [37, 38].

IPS has never been implemented within an offending population in the UK, and only one similar ongoing study within the United States (US) exists, so little is known about its efficacy within a criminal justice setting. Consequently, the current project is highly distinctive. Firstly, it will examine the impact of IPS within an offending population for the first time in the UK. Secondly, it is innovative in that it will examine the impact IPS has on an individual’s mental health, social stability, and recidivism within one inquiry, using both quantitative and qualitative techniques. Thirdly, the RE approach enables the study to go beyond hypothesis-testing to elaborate causal explanations for what works for whom.

### Recruitment

This research was initially designed for delivery in Her Majesty’s Prison Service (HMPS) across three prisons. However, in order to maximise referrals onto IPS and the current study participants will be recruited from a total of seven prisons and from offenders serving community orders. Community referrals onto IPS will be taken via Integrated Offender Management (IOM). The IOM is part of a multidisciplinary team that looks after ex­offenders in the community and includes, for example, the National Probation Service (NPS), Police, and Drug and Alcohol Teams.

### Research questions

How is the IPS intervention working in practice? What exactly does the IPS methodology intervention consist of to be able to continue and work effectively within a criminal justice setting?Is the IPS intervention successful in achieving competitive employment outcomes for ex-prisoners with mental health problems?What is the effect of the IPS intervention on the mental health of ex-prisoners who have a mental illness?What is the effect of the IPS intervention on the social stability of ex-prisoners who have a mental illness?What is the effect of the IPS intervention on the re­offending rates of ex-prisoners who have a mental illness?As a result of the above findings, how does IPS need to be adapted, if at all, to achieve the best possible outcomes in a criminal justice setting?

### Principal inclusion criteria

Aged between 18 and 65Able to give informed consentOffered employment support through the IPS serviceWithin 3 months of release date if in prison, if already released, within 6 months of release dateHave a SMI

SMI is defined as meeting one or more of the following criteria:Been treated by a psychiatrist in the last 12 monthsRecently been treated by a general practitioner for chronic mental health problems and/or substance misuse difficultiesBeen in hospital in the last 2 years due to mental health problemsCurrently on the caseload of their community mental health and/or substance misuse teamBeing treated by a mental health prison in­reach team and/or on a drug intervention programmeBeing treated in the community by a primary mental health team

Staff participants recruited in prison and in the community:To be eligible for the current study participants must be able to give informed consent and be either involved in IPS in some form or in the overall care of participants.

### Principal exclusion criteria

Offender participants recruited from prison and the community:Due to the nature of the intervention, those who might not adequately understand verbal explanations or written information given in English.

### Primary and secondary outcome measures

The primary outcome measure for the study is:

Employment gained in a competitive market through the IPS intervention (yes/no).

The secondary outcome measures for the study are:

Mental health, motivation to work, social stability, admissions to a psychiatric hospital, and offending behaviour

This will be assessed at 6 and 12 month intervals. The following information will also be collected where relevant:Time (days) until first competitive employmentJob tenure of competitive employment (hours/days/weeks/months worked from start of IPS)Job stability (working hours/contract gained)Income from employment

Leaving the study for any reason will be measured to assess any bias in the results.

Participant medical records­ hospitalisations, and the reasons for these, will be sought to fully understand the primary and secondary outcomes. Previous hospitalisations predict and increase the chance of future hospitalisation [39] and therefore may interrupt employment or the potential to gain employment during the study.

This medical information will also be very important when examining the mental health and motivation to work of participants throughout the study. By understanding if the participant has had any very recent previous and current hospitalisations, and why, the researcher can control for how this may mediate time until employment, participant dropouts, job tenure, and hours worked.

Information will also be sought from the participants’ prison records. Prison records would reveal any history of offending, index offence information, and the duration of sentence/community order. This information will also be important when examining any barriers a participant may have had when seeking competitive employment.

## Methods/Design

### Sample size and power

This is a novel piece of research examining how IPS works and develops within a criminal justice setting by means of a Realistic Evaluation (RE). It will yield valuable information for future studies, including the rates of recruitment and retention of participants, as well as the variation in the outcome measures, which is needed to undertake sample size calculations. The current sample size has been determined by the time and resources available: 20 (IPS) and 20 (No IPS) will have a power value of .60 and a critical z score = 1.645 [40] 1.

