### Offender interviews

Previous research indicates that the employment rate of offenders released from prison is 25 % [9]. The IPS literature consistently demonstrates that participation in IPS doubles the percentage of people in paid employment [41]. However, this excludes offenders who, for reasons cited earlier, face additional obstacles to employment. Therefore, in consideration of previous IPS research and the experience of the research team, an estimated hypothesis for the primary outcome is that 40 % of those on IPS will work at least one day in paid employment compared with 25 % for those who do not take part in IPS: at least eight of the intervention group of 20 will obtain work, as compared to five of the control group. A 15 % net increase in the competitive employment rate is both clinically and socially meaningful as not only would this reduce the range of costs to society that are associated with this population, but according to previous findings employment can have a positive impact on each individual’s life satisfaction and their mental health, especially if this is sustained [37, 38].

As there is no randomisation with regards to who takes part in IPS and who does not take part in IPS, motivation to gain employment will be measured, making it possible to control for the effect of differences in motivation on outcomes using logistic regression.

Given that the majority of recruitment and consent will be taken within prison the research team estimate that most (80 %) of those approached to participate in the research will take part. Furthermore, as not everyone who is approached will take part in the research, even though they may take part in IPS, it is believed that 36 people within each group will need to be approached.

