### Quantitative data

To determine whether there was a significant difference between those who took part in IPS and those who did not, concerning whether competitive employment was gained, a Chi-square analysis will be carried out at the six and 12 month intervals. Similarly, a logistic regression will also be carried out at these intervals in order to control for a participants’ motivation to work and assess covariates (e.g. age, gender, criminality) between both groups. Motivation to work will be controlled for during all comparisons, as the decision to seek employment is a personal choice.

Questionnaires pre and post IPS will be analysed using statistical independent sample t­tests, using a Statistical Package for the Social Science (SPSS) software, to determine whether overall significant improvements exist within mental health and social stability between those who did, and those who did not take part in IPS. A case by case examination of client yes/no responses in interviews, social stability measures (job contract and income, accommodation, social network etc.), and structured aspects within social stability questionnaires will be examined in conjunction with all other data, such as themes gained from interviews, to supplement all research questions and to make improvements and recommendations concerning IPS. Unemployment rates, jobs created data, fidelity to the IPS model and any changes in crime rates for particular areas will also be taken into account when examining results.

Descriptive data will be produced to meet the additional secondary outcomes; employment outcomes achieved. All other structured information from the relevant validated measures will be examined case by case for patterns of change amongst those who were part of IPS in comparison with those who were not part of IPS. Appropriate statistical analyses will account for any attrition variation between the IPS and no IPS control condition across the three data collection points. Missing data will also be excluded using the appropriate statistical techniques.

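### The critical z of 1.645 in the power statement is not reconciled with the non-directional chi-square planned for the primary outcome, and the power tied to it does not carry over

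*Protocol article*

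**What the plan says.** The protocol article, under Sample size and power, states that "20 (IPS) and 20 (No IPS) will have a power value of .60 and a critical z score = 1.645". It explains that the numbers were set by time and resources. It does not call the critical value one-sided or two-sided and names no alpha. The sentence ends with a citation and a footnote marker; the footnote text is not in the copy available for review.

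Under Offender interviews, the expectation for the primary outcome is directional: "40 % of those on IPS will work at least one day in paid employment compared with 25" per cent without it, spelled out as "at least eight of the intervention group of 20 will obtain work, as compared to five of the control group".

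Under Quantitative data, the purpose of the primary comparison is put this way: "To determine whether there was a significant difference between those who took part in IPS and those who did not". The method is that "a Chi-square analysis will be carried out at the six and 12 month intervals". No alpha, critical value or sidedness is given there. The 1.645 is the only significance threshold in the document.

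**The concern.** A chi-square on a 2x2 table rejects for a difference in either direction. A critical z of 1.645 belongs either to a one-sided test at 5% or to a two-sided test at 10%. Each way of joining the two sections leaves something to correct:

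- If 1.645 means one-sided 5%, the ordinary chi-square p-value does not implement it; the sign must be checked and the p-value halved.
- If 1.645 means two-sided 10%, the sections agree, but the study has adopted a 10% level without saying so.
- If the chi-square is read at the conventional two-sided 5%, the 1.645 does not belong to the planned test, nor does any power figure computed from it.

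With 20 per group, some plausible tables fall between 1.645 and 1.96. For those tables the conclusion on the primary outcome depends on a reading that the document leaves open. The allocation is not randomised, which is a further reason to fix the rule before the data are seen.

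**Working it through.** **Inputs.** n = 20 per group and critical z = 1.645 (Sample size and power); rates of 40% and 25%, expected counts of 8 and 5 (Offender interviews); chi-square without a stated level (Quantitative data). The two-sided 5% level is my assumption.

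**1. What 1.645 corresponds to.** The one-sided 5% point of the normal distribution is 1.645, and so is the two-sided 10% point. The two-sided 5% point is 1.960. On the chi-square scale with 1 df, 1.645² = 2.71 and 1.96² = 3.84.

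**2. The plan's own power figure.** With the pooled variance under the null and p̄ = (0.40 + 0.25)/2 = 0.325:

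- SE₀ = √(2 × 0.325 × 0.675 / 20) = 0.1481
- SE₁ = √(0.40 × 0.60/20 + 0.25 × 0.75/20) = 0.1462
- power = Φ[(0.15 − c × SE₀)/SE₁]

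| Method | c = 1.645, one-sided | c = 1.96, two-sided |
|---|---|---|
| Pooled null variance | Φ(−0.641) = 0.261 | Φ(−0.960) = 0.169 |
| Unpooled variance | 0.268 | 0.175 |
| Arcsine | 0.266 | 0.173 |
| Exact binomial | 0.266 | 0.179 |

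The stated .60 does not reproduce under either rule. For 60% power at 40% against 25%, about 71 per group would be needed one-sided and 96 two-sided (83 and 109 with continuity correction). A standardised effect of 0.60 with 20 per group and z = 1.645 does give 0.600, so a generic one-sided calculation may lie behind the figure. The document states no such effect, so this is only a possible explanation.

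**3. Tables on which the readings disagree.** The pooled z is (a − b)/20 divided by √(p̄(1 − p̄) × 2/20), with p̄ = (a + b)/40. It is the signed square root of the uncorrected chi-square. For 11 against 5, p̄ = 16/40 = 0.40, the SE is √(0.024) = 0.1549, and z = 0.30/0.1549 = 1.936.

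| IPS v control | z | chi-square | one-sided p | two-sided p |
|---|---|---|---|---|
| 8 v 5 (expected) | 1.013 | 1.03 | 0.156 | 0.311 |
| 10 v 5 | 1.633 | 2.67 | 0.051 | 0.102 |
| 11 v 5 | 1.936 | 3.75 | 0.026 | 0.053 |
| 12 v 5 | 2.239 | 5.01 | 0.013 | 0.025 |
| 8 v 3 | 1.771 | 3.13 | 0.038 | 0.077 |
| 9 v 4 | 1.688 | 2.85 | 0.046 | 0.091 |
| 12 v 6 | 1.907 | 3.64 | 0.028 | 0.057 |

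The rows 11 v 5, 8 v 3, 9 v 4 and 12 v 6 pass 1.645 but fail 1.96.

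**4. How often this happens.** This uses exact enumeration of all tables with two independent binomials of size 20.

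| True rates (IPS, control) | P(z beyond 1.645, IPS better) | P(z beyond 1.96, IPS better) | Between the cut-offs |
|---|---|---|---|
| 40%, 25% | 26.6% | 17.7% | 8.9% |
| 50%, 25% | 49.0% | 37.5% | 11.5% |
| 25%, 25% | 5.2% | 2.6% | 2.6% |

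At 40% against 25%, 8.9/26.6, or about one third, of the results that favour IPS at 1.645 would not reach 1.96.

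**5. False positives when 1.645 is applied to the chi-square.** With 25% in both groups, the exact chance of |z| ≥ 1.645 in either direction is 10.4%. For |z| ≥ 1.96 it is 5.1%.

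**The case against.** The strongest reply is that the document contains one threshold, not two. The analysis section states no level, so a reader might infer that a borderline result is positive under one section and negative under the other, but the text does not say that. The negative verdict appears only when a conventional 5% is brought in from outside. Read as two-sided 10%, the chi-square would reject at 2.71 and the two sections would agree exactly. A one-sided reading is coherent too: the expectation is directional, and checking the sign of the difference turns the chi-square into a one-sided test. The missing footnote may say which was meant. A condensed article may also leave the significance level to a fuller document.

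All of this stands against the stronger reading. It is also true that the expected 8 against 5 is non-significant under every rule, that the rules agree in about 91% of cases at 40% against 25%, and that the chi-square is accompanied by a logistic regression adjusting for motivation.

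It does not dispose of the point. The issue is not that a level is absent, but that a critical value is printed which fits the planned test only at an undeclared 10% level or with an undeclared one-sided rule. The power printed beside it does not follow from the stated rates under either reading.

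**Conclusion.** The mismatch is real and should be corrected, but it is one of reconciliation and not a pair of opposed decision rules. The protocol's only threshold is one-sided 5% or two-sided 10%; its primary test is non-directional with no level given. If 1.645 governs the chi-square, the two-sided error is about 10.4% (assuming 25% employed in both groups). If a conventional two-sided 5% governs, 1.645 is the wrong value, and at the planned rates 8.9% of possible results favour IPS at one cut-off but not at the other.

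The power statement needs correction on either reading: about 0.26 to 0.27 at 1.645 and 0.17 to 0.18 at two-sided 5%, against the stated .60. These figures assume 20 analysed per group, independent participants and the uncorrected chi-square. The content of the missing footnote is unknown; it could settle the sidedness, but it would not make .60 follow from 40% against 25% with 20 per group.

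**What to change.** State one alpha and its sidedness for the primary comparison, and use it under both Sample size and power and Quantitative data. Two-sided 5% (|z| = 1.96, chi-square 3.84), reported with a 95% confidence interval for the difference in employment rates, fits the chi-square already planned. If the authors intend a one-sided 5% or a two-sided 10% rule, they should say so in both places and give the reason.

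Do not only replace 1.645 by 1.96, because .60 would then stand beside a threshold that it fits even less well. Restate the power for 40% against 25% with 20 per group under the chosen rule: about 0.17 to 0.18 at two-sided 5%. If .60 was computed for some other effect, name that effect.

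The change takes a line or two in each section and alters no design feature, since the sample size rests on time and resources. The cost is a less favourable stated power.

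### The stated power of .60 is not the power for the plan's only stated primary-outcome effect (40% vs 25%), which is about 0.26 at the stated critical z

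*Protocol article*

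**What the plan says.** Under Sample size and power, the protocol article explains that available time and resources fixed the sample size, and then states that "20 (IPS) and 20 (No IPS) will have a power value of .60 and a critical z score = 1.645". The sentence carries a citation and a footnote marker. It gives no effect size, and no alpha or sidedness in words.

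The next section, Offender interviews, gives the hypothesis for the primary outcome: "40 % of those on IPS will work at least one day in paid employment compared with 25" per cent without IPS. It turns this into counts, "at least eight of the intervention group of 20 will obtain work, as compared to five of the control group", and adds that "A 15 % net increase in the competitive employment rate is both clinically and socially meaningful".

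The primary outcome is binary (Primary and secondary outcome measures). Under Quantitative data, a chi-square test at six and 12 months is planned "To determine whether there was a significant difference between those who took part in IPS and those who did not", with no significance level given.

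**The concern.** A reader who meets a power figure and then, in the next section, the one hypothesis for the primary outcome will naturally put the two together. Together they do not agree: a 15-point difference is small for 20 per group, and .60 is far above what that comparison can deliver.

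What is at stake is how the result is weighed. With power near 0.26, a non-significant chi-square is the likely outcome even if the investigators' hypothesis is exactly right. A reader who believes the power is .60 will give that result more weight against IPS than it can bear. The same section offers the study as a source for later sample size calculations, so a power figure detached from its effect could also mislead later planning.

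**Working it through.** **Inputs from the article.** n = 20 per group and critical z = 1.645 (Sample size and power); p1 = 0.40, p2 = 0.25 (Offender interviews); chi-square test of a yes/no outcome (Quantitative data).

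**1. What reproduces .60.** For a standardised effect d with n per group, power = P(Z > 1.645 − d·√(n/2)). Setting power to .60 gives d = (1.645 + 0.2533)·√(2/20) = 0.600. So .60 is coherent for a standardised effect of 0.60. On the proportion scale (Cohen's h = 0.60), with 25% in the control group, this means an IPS rate of about 54% (0.538 by arcsine, 0.542 by the pooled formula).

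**2. Power for the stated hypothesis at z = 1.645.**
- Mean proportion = 0.325. SE under the null = √(2 × 0.325 × 0.675/20) = 0.1481. SE under the alternative = √((0.40 × 0.60 + 0.25 × 0.75)/20) = 0.1462.
- Pooled: Φ((0.15 − 1.645 × 0.1481)/0.1462) = Φ(−0.640) = 0.261.
- Unpooled: Φ(0.15/0.1462 − 1.645) = 0.268.
- Arcsine: h = 0.322, and Φ(0.322·√10 − 1.645) = 0.266.
- Exact enumeration of the uncorrected test: 0.266.
- More conservative tests give less: continuity-corrected 0.163, one-sided Fisher 0.177.

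**3. If the chi-square is run at two-sided 5% (assumed; z = 1.96).**
- Pooled: Φ((0.15 − 1.96 × 0.1481)/0.1462) = Φ(−0.960) = 0.169.
- Arcsine 0.173, unpooled 0.175, exact 0.179. Continuity-corrected 0.097, Fisher 0.109.
- At two-sided 10%, where the critical z is again 1.645, power is about 0.26 to 0.27.

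**4. Other inputs in the article, tried as explanations of .60 (pooled formula, z = 1.645).**

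| Input | Power |
|---|---|
| 50% vs 25% (IPS doubling the rate), n = 20 | 0.495 |
| 60% vs 25%, n = 20 | 0.737 |
| 61% vs 23%, n = 20 | 0.804 |
| 40% vs 25%, n = 36 (number to be approached) | 0.386 |

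None gives .60. The nearest is 60% vs 25% at two-sided 5%, with 0.617, but that uses z = 1.96 and not the stated 1.645.

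**5. The hypothesised result itself.** For 8/20 vs 5/20, z = 0.15/0.1481 = 1.01, chi-square = 1.03, two-sided p = 0.31. The 95% confidence interval is 0.15 ± 1.96 × 0.1462 = 0.15 ± 0.287, or about −14 to +44 points. With 5/20 in the control group, 10/20 gives z = 0.25/0.1531 = 1.633 and still misses 1.645; 11/20 passes.

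**6. Size needed for .60 at 40% vs 25%.** About 71 per group at z = 1.645 (70 by arcsine), or 96 per group at two-sided 5%, without continuity correction.

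**The case against.** The best defence is that the article never says .60 is the power for 40% vs 25%. The hypothesis stands under a different heading, and the footnote to the power sentence is not shown. A standardised effect of 0.60 reproduces the figure exactly. This stands in part. A reader might infer that the authors put 40% vs 25% into a formula and made an arithmetic slip, or that the article expressly promises to detect that difference six times in ten. The text supports neither. It does show a power figure with no effect attached, beside a stated primary hypothesis to which the figure does not apply. Whatever the footnote says, .60 is not the power for 40% vs 25%.

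A reader might also infer that the article contradicts itself on sidedness, because 1.645 is the one-sided 5% value and a chi-square is non-directional. That is not established. No alpha is stated in words, and 1.645 is also the two-sided 10% value, at which the chi-square has power of about 0.26 to 0.27. The figure of 0.17 is therefore conditional on a level the article does not give.

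Finally, resources set the sample size, .60 is itself an open admission of low power, and the realistic evaluation combines qualitative and quantitative evidence before interpretation. All this is true. It means that the correction leaves the sample size alone, and that no passage plans to read a non-significant test as proof that IPS fails. It does not make the power figure right for the stated hypothesis.

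**Conclusion.** The point holds in this form: for the only effect stated for the primary outcome, 20 per group at z = 1.645 has power of about 0.26, not .60. The stated figure is more than twice the computed one (0.60/0.26 = 2.3), and the choice among standard two-group formulas does not close the gap.

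The computed figure assumes two independent groups with all 20 per group analysed, an unadjusted comparison and no continuity correction. The article gives no dropout rate. Losses would lower the power, and the planned adjustment for motivation could change it. The origin of .60 cannot be settled from the text shown.

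The finding does not support a larger sample as a necessary remedy, nor replacing the planned significance test with estimation. The first was ruled out by resources, and the second would be a preference about the analysis and does not follow from the error.

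**What to change.** Keep 20 + 20. In Sample size and power, replace .60 with the power for 40% vs 25%: about 0.26 at z = 1.645, or about 0.17 if the chi-square is to be run at two-sided 5%. If .60 was meant for another effect, name that effect and say that it is not the primary-outcome hypothesis.

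State one alpha and sidedness, and use it both for the power statement and for the chi-square under Quantitative data.

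Report the difference in employment proportions with its 95% confidence interval alongside the planned test. At the hypothesised result this runs from about −14 to +44 points.

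The changes are to wording and reporting. Recruitment, data collection and the planned test stay as they are. The cost is that the stated power becomes less favourable.
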